#### Sample size {14}

The sample size was calculated to be 95 patients per study arms A and B. This was done taking into account the following criteria: power = 80%, *α* = 5%, response rate standard care = 0.5 [1, 2] and response rate PGx guided = 0.7 [16]. For the observational study arm, there is no sample size calculation needed, since this arm does not contribute to the primary endpoint.

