### Statistical methods

#### Statistical methods for primary and secondary outcomes {20a}

The primary outcome of this study is the response rate at day 28 in study arms A and B. The response is defined as a reduction of the HAM-D17 score of at least 50% compared to baseline at day 0. Additionally, the following secondary outcomes are assessed: time to response, remission rate, overall change in HAM-D17 score, laytime in the clinic, change in BDI-II score, change in FIBSER score, and number of AEs related to antidepressant pharmacotherapy. For statistical analyses, the software packages of “IBM SPSS Statistics” and “GraphPad Software” are used. A descriptive statistics analysis for all variables is performed. Fisher’s exact test or *t* test is used to compare pairwise differences between groups and between baseline and follow-up visits as per data type. To measure the correlation between variables, the Spearman coefficient will be used. Significance level is two-sided, *α* = 0.05. For further statistical analyses, adjustments for confounding factors will be taken into account. Any deviation from the original statistical plan will be described and justified in the final trial report.

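### The stated 80% power at 95 per arm is not met by Fisher's exact test, the only test the protocol names for a binary endpoint; its exact power is 76.0%

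*Protocol article*

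**What the plan says.** Sample size {14} reads: "The sample size was calculated to be 95 patients per study arms A and B". The inputs listed are "power = 80%, *α* = 5%, response rate standard care = 0.5" and "response rate PGx guided = 0.7". The section names neither a test nor a formula.

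Statistical methods for primary and secondary outcomes {20a} makes the endpoint binary: "The primary outcome of this study is the response rate at day 28 in study arms A and B", with response defined as a HAM-D17 fall of at least half from day 0. On testing, it says: "Fisher’s exact test or *t* test is used to compare pairwise differences between groups and between baseline and follow-up visits as per data type". On the level, it says: "Significance level is two-sided", with alpha 0.05. No other test for a binary outcome appears in the article.

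Two other sections bear on the calculation. Trial design {8} gives equal allocation. The section on non-adherence and missing data {20c} replaces drop-outs until each arm holds 95, so 95 is the number to be analysed and there is no reserve.

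**The concern.** The sample size and the analysis belong to different tests. Fisher's exact test is conservative for a two-arm comparison of proportions: its actual type I error lies below the nominal 5%, and it pays for that in power. A size taken from an uncorrected approximation therefore falls short of its target power when the data are analysed with Fisher's test.

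What is at stake is the power claim for the primary hypothesis. If Fisher's test is used, the risk of missing the assumed difference of 20 percentage points is higher than the protocol states, and part of the 5% alpha goes unused. The article also leaves open which of the two statements, the power or the test, its authors would give up.

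**Working it through.** **Inputs.** Control rate 0.5, intervention rate 0.7, power 80% and alpha 5% from {14}; two-sided level from {20a}; equal allocation from {8}; 95 analysed per arm from {20c}. Normal quantiles: 1.960 for two-sided 5% and 0.842 for 80% power, so (1.960 + 0.842)² ≈ 7.849. Difference 0.2, squared 0.04. Mean rate 0.6.

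**Step 1: reproduce 95.**

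- Pooled variance under the null, separate variances under the alternative: n = [1.960·√(2·0.6·0.4) + 0.842·√(0.5·0.5 + 0.7·0.3)]² / 0.04 = (1.358 + 0.571)² / 0.04 ≈ 93.0, so 93.
- Pooled variance under both hypotheses: n = 2·0.6·0.4·7.849 / 0.04 = 94.2, so 95, an exact match.
- Arcsine: 92.7, so 93.
- Unpooled variance: 0.46·7.849 / 0.04 = 90.3, so 91.
- Continuity-corrected, which approximates Fisher's test: n = (93/4)·[1 + √(1 + 4/(93·0.2))]² ≈ 102.8, so 103.
- One-sided: 74 uncorrected, 83 corrected.

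The stated size thus fits a two-sided calculation without continuity correction. The corrected formula gives 8 more per arm.

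**Step 2: exact power at 95 per arm.** For each pair of response counts (x in the control arm, y in the intervention arm, each 0 to 95), decide whether the test gives p ≤ 0.05. Then sum Bin(x; 95, 0.5) × Bin(y; 95, 0.7) over the rejected pairs. The two-sided Fisher p-value adds up all tables, given the margins, that are no more probable than the observed one.

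| Test at 95 per arm, two-sided 0.05 | Exact power |
|---|---|
| Fisher's exact | 76.0% |
| Chi-square with continuity correction | 76.0% |
| Fisher, mid-p version | 80.1% |
| Pearson chi-square, uncorrected | 80.6% |

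**Step 3: size needed with Fisher's test.**

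| n per arm | Fisher power |
|---|---|
| 95 | 76.0% |
| 100 | 79.2% |
| 101 | 79.9% |
| 102 | 80.6% |

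The 80% target is first met at 102 per arm, that is 204 in total instead of 190: 7 more per arm, and 7/95 ≈ 7%.

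**Step 4: actual type I error at 95 per arm**, for common response rates from 0.3 to 0.7: Fisher about 3.3% to 3.5%; uncorrected Pearson about 4.85% to 5.03%.

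**The case against.** The strongest reply is that the gap is small and on the safe side. Four points of power equal 7 patients per arm, and an intervention rate of about 0.71 in place of 0.70 would bring Fisher's test back to 80% at 95 per arm. The rates 0.5 and 0.7 are round values taken from cited studies, and their uncertainty is surely larger than 0.01. Sizing by a normal approximation and analysing with Fisher's test is common practice, and a positive result would remain valid. All of this stands, and it limits the weight of the point. It does not make the stated 80% true for the named test.

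A second reply is that {20a} never assigns Fisher's test to the primary endpoint in so many words. Its sentence covers all comparisons by data type, and a separate analysis plan may say more. That lowers certainty a little. Still, the primary outcome is binary and Fisher's is the only test for such data in the article.

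Three stronger readings are tempting, and the documents do not support them:

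- A reader might infer that 95 is an arithmetic error. It is not: step 1 reproduces it, and {14} ties it to no test.
- A reader might infer that 95 fits the uncorrected chi-square test and nothing else. The arcsine formula and the mid-p version of Fisher's test fit too, although the protocol names neither.
- A reader might infer that a centre-stratified Mantel-Haenszel test would also give 80.6%. That figure was computed for the unstratified Pearson test. A stratified figure would need centre sizes and centre-specific rates, which the article does not give.

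**Conclusion.** The point holds as a moderate inconsistency between {14} and {20a}. On the plan's own assumptions, the named test gives 76.0% power where 80% is stated: a type II error of 24% in place of 20%, or a shortfall of 7 patients per arm. Type I error is not inflated, and no estimate is affected by this mismatch.

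The result assumes that the data-type rule in {20a} governs the primary endpoint, that the test is two-sided at 0.05 as written, that exactly 95 per arm are analysed, and that the rates are 0.5 and 0.7. Sidedness matters: a one-sided Fisher test at 0.05 would have 85.0% power, but {20a} excludes it.

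**What to change.** Choose one of two changes.

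1. Keep Fisher's exact test and restate the power in {14} as 76% for 95 per arm. This changes one figure and leaves the analysis alone.
2. Name the Pearson chi-square test without continuity correction as the primary test in {20a}. Its exact power at 95 per arm is 80.6%, so {14} can stand.

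The second change needs more care. Recruitment began in September 2020, the HAM-D17 raters are not blinded to allocation ({18a}), and interim analyses are allowed at times not set in advance ({21b}). A move to a less conservative test should therefore be documented as an amendment and made before any comparative data are examined. If such data have already been seen, the first change is the cleaner one. The statistical cost of the second is small: its exact size is about 4.85% to 5.03% for common rates of 0.3 to 0.7, marginally above 5% at some of them.

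Neither change requires more patients. Keeping both Fisher's test and 80% power would require 102 per arm.

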#### Recruitment {15}

Participants are recruited and screened for eligibility by the treating investigator in daily clinical practice, during the regular hospital admission interview, when entering the clinic for an inpatient stay.

### Assignment of interventions: allocation

#### Sequence generation {16a}

Allocation of participants to study arms A or B is based on a computer-generated allocation sequence without any stratifying factors (static unstratified multi-block randomization).

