### Trial design {8}

This is an open-label, randomized controlled trial, investigating the effectiveness and tolerability of registered antidepressants in adult inpatients with diagnosed major depressive episode.

To prevent selection bias, eligible patients in need of a new antidepressant pharmacotherapy are randomized at the same ratio into either the control or the intervention arm (parallel study arms).

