## Methods: Participants, interventions, and outcomes

### Study setting {9}

This is a multicenter clinical trial conducted in Switzerland, at the Psychiatric Clinic of the Solothurner Spitäler AG in Solothurn and the Private Clinic Wyss in Münchenbuchsee.

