#### Implementation {16c}

Separated departments conduct each process of generating the allocation sequence, enrolling the participants, and assigning participants to interventions. The allocation sequence is implemented by an independent data management team of the clinical trials unit at the University of Basel in Basel, Switzerland. The investigators at the Psychiatric Clinic in Solothurn and Private Plinic Wyss in Münchenbuchsee, in Switzerland, conduct the enrolment of participants. Furthermore, the responsible clinical pharmacists of the Solothurner Spitäler AG association perform randomization electronically.

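### Two clinics share an unstratified sequence and centre is absent from the analysis: valid and unbiased, but a prespecified centre-stratified comparison would remove avoidable chance variation at no cost in patients

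*Protocol article*

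**What the plan says.** All references are to the Protocol article.

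- **Study setting {9}**: the trial runs "at the Psychiatric Clinic of the Solothurner Spitäler AG in Solothurn and the Private Clinic Wyss in Münchenbuchsee", that is, in a clinic of a hospital group and in a private clinic.
- **Trial design {8}**: patients who need a new antidepressant are "randomized at the same ratio into either the control or the intervention arm (parallel study arms".
- **Sequence generation {16a}**: allocation is "based on a computer-generated allocation sequence without any stratifying factors (static unstratified multi-block randomization". I read this as one sequence serving both clinics, since a list per clinic would be stratification.
- **Sample size {14}**: "The sample size was calculated to be 95 patients per study arms A and B", from "response rate standard care = 0.5", "response rate PGx guided = 0.7", 80% power and a 5% level.
- **Statistical methods {20a}**: groups are compared by Fisher's exact test or a t test according to data type. "Significance level is two-sided", at 0.05. Centre is not mentioned. Adjustment for confounders is foreseen only for further analyses, and no factor is named.
- **Additional analyses {20b}**: no subgroup or adjusted analysis is planned at present.

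The article gives no reason for leaving centre out. Because {20b} rules out adjustment for now, this is a stated choice and not simply a detail left to an analysis plan that is not shown.

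**The concern.** Blocks keep the overall arm totals close to 1:1. When two clinics draw from the same sequence, each block is filled by whichever clinic enrols next, so the blocks do not balance the arms within a clinic. One arm can by chance hold more patients from one clinic. If response also differs between clinics, that imbalance moves the observed difference between the arms, and a comparison that ignores centre cannot take it out again.

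A clinic difference in measured response is plausible. Section {18a} has HAM-D17 scored by the treating physician or designated staff who know the allocation, and in arm B the treating physician alone chooses the drug. The article does not document any such difference. What is at stake is precision, and how easily a reader can trust a result from unequal clinic mixes.

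**Working it through.** **Inputs.** From the article: 95 per arm, 190 in total; response 0.5 and 0.7; two-sided 5%; 80% power; two clinics. Assumed, because the article does not give them: clinic split (50:50, 70:30, 80:20), gap in response between clinics (0, 20, 30 points), block sizes (4 and 6 mixed), and a random order of enrolment between the clinics.

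**Step 1: the plan's sample size.** n = [1.960·√(2·0.6·0.4) + 0.842·√(0.25 + 0.21)]² / 0.20² = (1.358 + 0.571)² / 0.04 ≈ 93 per arm. The plan's 95 is within two patients of this, and power at 95 by the same formula is 0.808. The stated figure is reproduced.

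**Step 2: chance imbalance in clinic share.** With K of 190 patients from clinic 1 and 95 in each arm, the number from clinic 1 in arm A is hypergeometric, with variance 95·(K/190)·(1 − K/190)·(95/189). The between-arm difference in share, d, has SD = 2·SD(count)/95.

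| Split | SD(count) | SD(d) | P(abs d ≥ 10 points) | P(abs d ≥ 15 points) |
|---|---|---|---|---|
| 50:50 | √11.94 = 3.46 | 7.3 points | 0.147 | 0.042 |
| 70:30 | √10.03 = 3.17 | 6.7 points | 0.113 | 0.026 |

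A simulation with an unstratified block list (4,000 runs per scenario, splits from 50:50 to 80:20) agrees: mean zero, SD 5.8 to 7.3 points, 95th percentile of the absolute difference 12 to 15 points.

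**Step 3: effect on the primary difference.** Shift = clinic gap × d. With an assumed 20-point gap and a 50:50 split, the SD is 0.20 × 7.27 = 1.45 points, and 1.96 × 1.45 ≈ 2.9 points. Across the simulated splits the 95th percentile was 2.3 to 2.9 points, and 3.5 to 4.4 points with a 30-point gap.

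**Step 4: set against total sampling error.** SE = √(0.25/95 + 0.21/95) = √(0.46/95) = 6.96 points, so 1.96·SE = 13.6 points. The centre shift is contained in this. With the 20-point gap and a 50:50 split, the clinic rates are 0.4 and 0.6 in control and 0.6 and 0.8 in PGx. The within-clinic variances average 0.24 and (0.24 + 0.16)/2 = 0.20. Then SE = √(0.44/95) = 6.81 points, or ±13.3. The variance removed is 0.02/95, whose root is 1.45 points, matching step 3. It is 0.02/0.46 ≈ 4% of the total.

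**Step 5: behaviour of the tests (same simulation, unstratified list).**

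| | Fisher, unadjusted | Mantel-Haenszel, stratified by centre |
|---|---|---|
| Type I error | 0.031 to 0.040 | 0.047 to 0.054 |
| Power | 0.75 to 0.78 | 0.80 to 0.85 |

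The power difference is about 4 points with no clinic gap at all, 5 to 6 points with a 20-point gap, and 7 to 8.5 points with a 30-point gap. The first 4 points reflect Fisher's conservatism (its exact power at 95 per arm is 0.760) and have nothing to do with centre.

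**The case against.** The strongest case for leaving the plan alone has four parts.

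1. **Validity is not in question.** Unstratified 1:1 randomisation is unbiased, and an unadjusted test fits an unstratified list. This stands. A reader might infer that clinic differences bias the result or raise the false-positive rate. Neither follows: the imbalance averages zero, the ordinary standard error already covers it, and simulated type I error stayed below 5%.
2. **The sizes rest on assumptions.** This stands too. Without clinic-specific rates or an enrolment split, the ±3 points is an illustration.
3. **A shared list has a merit.** In an open-label trial with raters aware of allocation, the next assignment is harder to predict at either clinic when both draw on one list. That is a reasonable ground for not changing the list.
4. **Centre adjustment often belongs in the analysis plan.** This stands only in part, because {20b} says that no adjusted analysis is planned and the adjustment sentence in {20a} names no factor.

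Two further readings are tempting and unsupported. One is that the arm A service is in-house at one clinic and external at the other. Section {16c} says that "the responsible clinical pharmacists of the Solothurner Spitäler AG association perform randomization electronically", which covers randomisation, not delivery of the service, and section {33} speaks of the responsible pharmacist at the study site. The other is that the clinics differ in discharge practice. No section describes it, so no effect on length of stay can be sized.

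**Conclusion.** The point holds as a matter of efficiency. The article fixes both an unstratified sequence over two clinics and a comparison without centre, so chance differences in clinic mix (SD about 6 to 7 points) stay in the primary result. Under an assumed 20-point clinic gap they account for random error of about ±3 points, some 4% of the sampling variance. Removing them would narrow the 95% half-width from about 13.6 to 13.3 points. With a 30-point gap the gain is larger; with no gap there is none. The primary conclusion is not threatened, and the whole power difference between the two tests should not be credited to centre. The reason to act is that the remedy uses data already held and is valid under the existing list.

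**What to change.** Before outcome data are examined, amend {20a} and {20b} together so that they agree and name centre:

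- **Primary endpoint:** compare response with centre as a stratum, by an exact stratified or Mantel-Haenszel test, and report a centre-stratified risk difference with its confidence interval. Choose one test in advance. The simulated power above belongs to the Mantel-Haenszel version without continuity correction; an exact test would be more conservative.
- **Continuous endpoints:** include centre in the models.
- **By-centre effects:** show them descriptively only. The trial is not sized to compare clinics.

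Timing matters because the interim analyses section {21b} allows looks at times not set in advance. If an analysis plan already contains centre, aligning these two sections is enough.

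The cost is one stratum in the analysis, with no change in sample size. Changing the randomisation list is optional and not needed. Recruitment began in September 2020, so a list per centre would affect only patients still to be randomised, and it would make allocation somewhat more predictable in an open-label trial.

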#### Concealment mechanism {16b}

Randomization for participant allocation into study arms A and B is performed by the appointed clinical pharmacist without knowledge of the allocation sequence, within the web-based electronic data capture program secuTrial® (interactive Systems GmbH, Berlin, Germany). This is an open-label study; however, the service of individual processing and evaluation of the genotyping data is only conducted by the respective clinical pharmacist for participants allocated to arm A (intervention arm) at baseline (day 0). To further guarantee blinding to the genotyping results, assessed during the run-in phase, only the appointed clinical pharmacists do have password-protected access to the genetic data from Stratipharm®.

#### Implementation {16c}

Separated departments conduct each process of generating the allocation sequence, enrolling the participants, and assigning participants to interventions. The allocation sequence is implemented by an independent data management team of the clinical trials unit at the University of Basel in Basel, Switzerland. The investigators at the Psychiatric Clinic in Solothurn and Private Plinic Wyss in Münchenbuchsee, in Switzerland, conduct the enrolment of participants. Furthermore, the responsible clinical pharmacists of the Solothurner Spitäler AG association perform randomization electronically.

### Assignment of interventions: blinding

#### Who will be blinded {17a}

This is an open-label study, hence no blinding of intervention allocation is possible and needed. However, the genetic data assessed during the run-in phase will only be shared with the treating physician and patients allocated to the control or observational group after day 28 of the treatment phase.

#### Procedure for unblinding if needed {17b}

Not applicable, as described in section {17a}, this is an open-label trial.

### Data collection and management

#### Plans for assessment and collection of outcomes {18a}

Outcomes described in section {12} are assessed and collected using validated questionnaires and scoring tools (HAM-D17, FIBSER, BDI-II). FIBSER and BDI-II are patient-self-rated scores where the patients fill the according questionnaires independently [19, 20]. The HAM-D17 score is assessed by a trained rater (e.g., treating physician or specifically designated personnel) [18] who is however, not blinded to the patient allocation. The treating physician does the antidepressant adverse event assessment and grading according to the CTCAE version 5.0 [21]. The described data is collected on paper forms approved by the local ethics committee or directly entered into the patient electronic medical record when appropriate.

#### Plans to promote participant retention and complete follow-up {18b}

Assessments and follow-ups are only conducted during the participants’ inpatient stay at the psychiatric clinic. Therefore, the risk of loss to follow-up and deviation to the protocol due to failure to comply with the study visits are considered negligible. However, patients who withdraw their consent (e.g., refuse further data collection) will be informed that all data collected until the time point of their withdrawal will be kept coded and used for analysis.

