#### Outcomes {12}

The primary endpoint is defined as the rate of response to the antidepressant therapy at the end of week 4 of the treatment phase. This time point was chosen based on the recommendations of the SGAD, which advise to assess clinical effectiveness after four weeks of antidepressant pharmacotherapy [3]. Moreover, the response is determined as a reduction in the Hamilton Depression (HAM-D) Scale score of at least 50% from the baseline score [18]. In this study, the 17-item HAM-D questionnaire (HAM-D17) is used.

Secondary endpoints will be assessed to further evaluate the clinical effectiveness of pharmacist-guided PGx testing as an intervention in antidepressant pharmacotherapy. Included are the following endpoints: (1) time to response—time span from the start of antidepressant pharmacotherapy until first assessed response (= HAM-D17 reduction of at least 50% compared to baseline), until end of week 4; (2) remission rate—HAM-D17 score ≤ 8, at week 4; (3) overall change in HAM-D17 score from baseline to end of week 4; (4) time till discharge—time span from admission to discharge from inpatient treatment, assessed up to 3 months; (5) patient depression self-rating—two weekly assessment with Beck-Depression-Inventory (BDI-II) questionnaire [19], until end of week 4; (6) side effect measure—weekly assessment of self-rated frequency, intensity, and burden of side effects (FIBSER score) [20], until end of week 4; and (7) Number of AEs related to antidepressant pharmacotherapy—severity grading ≥ 2 (using CTCAE version 5.0) [21] and causality to antidepressant pharmacotherapy assessed as possible, probable, or definite, until end of week 4.

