##### Randomization and procedures for arms A and B

If after the run-in phase, at day 0 (±3 days), the treating physician assesses the adjustment to a new antidepressant pharmacotherapy as necessary, and the patient is randomized to either arm A (intervention group) or arm B (control group) (see Fig. 1).

In arm B, the treating physician alone, according to the current standard of care considering clinical factors only, will determine the selection and dosing of the new antidepressant pharmacotherapy. The treating physician and patient will be blinded to the results of the previously conducted pharmacogenotyping for patients randomized to arm B until day 28. For patients in arm B, results from prior pharmacogenetic testing will be interpreted by a clinical pharmacist and made accessible to the treating physician after day 28.

In arm A, a clinical pharmacist will process and evaluate the results from PGx testing (Stratipharm®) in context of the individual patient history as well as current co-medication and forward an individualized recommendation for antidepressant selection and dosing to the treating physician at day 0.

In both arms, the newly prescribed antidepressant pharmacotherapy intake is continuously documented and therapy response observed over a period of 28 days with weekly assessments of adverse events related to the antidepressant medication (using CTCAE version 5.0) and scorings of HAM-D17 (days 0, 7, 14, 21, and 28; ±3 days) as well as patient self-assessments of FIBSER score (days 0, 7, 14, 21, and 28; ±3 days) and BDI-II score (days 0, 14, and 28; ±3 days) (see Table 1).

If patients in either study group remain in the clinic after day 28 (±3 days), a weekly follow-up of HAM-D17, FIBSER, and two-weekly BDI-II are continued until discharge (see Table 1).

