#### Methods in analysis to handle protocol non-adherence and any statistical methods to handle missing data {20c}

Missing data will be retrospectively retrieved from medical records if possible. If the missing data cannot be retrieved, the last observed value will be used for analysis. Study drop-outs are replaced to achieve the final calculated study size of 95 patients per study arms A and B.

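### Ratings are made only in hospital, so a patient discharged before about day 25 has no week-4 score, and the plan fills the gap with the last value or may replace the patient

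*Protocol article*

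**What the plan says.** - **Endpoint.** Section {12} on outcomes fixes the target: "The primary endpoint is defined as the rate of response to the antidepressant therapy at the end of week 4 of the treatment phase". Statistical methods {20a}: "The response is defined as a reduction of the HAM-D17 score of at least 50% compared to baseline at day 0". The day-28 rating has a ±3-day window (Randomization and procedures for arms A and B).
- **Where ratings are made.** Section {18b}: "Assessments and follow-ups are only conducted during the participants’ inpatient stay at the psychiatric clinic". From this alone the section infers that "the risk of loss to follow-up and deviation to the protocol due to failure to comply with the study visits are considered negligible".
- **Missing data.** Section {20c}, first step: "Missing data will be retrospectively retrieved from medical records if possible". Second step: "If the missing data cannot be retrieved, the last observed value will be used for analysis". The same section replaces drop-outs until there are 95 patients per arm.
- **Discharge.** Table 1 has an undated clinic-discharge column that includes a HAM-D17. Outcomes {12} lists as a secondary effectiveness endpoint "time till discharge—time span from admission to discharge from inpatient treatment, assessed up to 3 months", and Objectives {7} compares length of hospital stay between the arms.

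**The concern.** Inpatient-only assessment makes missed visits unlikely while the patient is in the clinic. It also means that observation stops at discharge. Section {18b} draws reassurance from the first fact and does not address the second.

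A patient discharged before about day 25 has no score in the day-28 window. If the records hold none, the analysis uses an earlier score, so the endpoint for that patient becomes response at the last inpatient rating. The protocol chose week 4 because it regards four weeks of exposure as necessary to judge response (Background {6a}, Outcomes {12}), so an earlier score does not serve that purpose. Single imputation also treats the filled value as if it had been observed.

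The trial lists discharge time among its effectiveness endpoints and compares it between arms. On its own terms, the intervention may change who still has a day-28 score. A difference in discharge timing or withdrawal could then appear as a difference in response, or hide one.

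**Working it through.** **1. Length of stay needed.** Consent and eligibility are at day −8 in Table 1, and recruitment is at admission (Recruitment {15}). An observed day-28 score therefore needs about 8 + 28 = 36 days in the clinic, or 8 + 25 = 33 days at the early edge of the window. The document gives no length of stay and no share of patients discharged before day 25.

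**2. The plan's own figure.** Inputs from Sample size {14}: 0.5 against 0.7, 80% power, α = 5%, two-sided according to {20a}. With pooled variance, n = 2 × 0.6 × 0.4 × (1.960 + 0.842)² / 0.2² = 94.2, so 95 per arm. The usual formula with unpooled variance under the alternative gives 93. The stated 95 reproduces and is not in dispute. With Fisher's exact test, which {20a} names for binary data, exact power at 95 per arm is 76.0%, and the rejection rate under a common true rate of 0.5 is 3.5%.

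**3. Bias from carrying forward.** In each arm let *m* be the share without a day-28 score, *q* the chance that the carried score counts as response, and *t* the true day-28 response chance in those patients.

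Observed rate = true rate + *m*(*q* − *t*)

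Bias in the difference = *m*_A(*q*_A − *t*_A) − *m*_B(*q*_B − *t*_B)

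This is zero when *m* and (*q* − *t*) are equal in both arms. All values of *m*, *q* and *t* below are assumptions, with *q* and *t* taken as the same in both arms.

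True rate 0.5 in both arms, Fisher's test, 95 per arm:

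| *m*_A | *m*_B | *q* | *t* | Bias (points) | Rejection rate |
|---|---|---|---|---|---|
| 0.10 | 0.10 | 0.9 | 0.7 | 0 | 3.5% |
| 0.20 | 0.10 | 0.9 | 0.7 | +2 | 4.2% |
| 0.20 | 0.10 | 0.9 | 0.5 | +4 | 6.2% |
| 0.30 | 0.10 | 0.9 | 0.5 | +8 | 15.7% |
| 0.20 | 0.10 | 0.3 | 0.5 | −2 | 4.2% |

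By size of bias alone: 3 points (0.53 against 0.50) gives 5.1%, and 5 points (0.55 against 0.50) gives 8.0%.

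True rates 0.7 and 0.5, with carried scores that miss later response (*q* = 0.5, *t* = 0.8):
- *m*_A = 0.20, *m*_B = 0.10: 0.70 − 0.06 = 0.64 against 0.50 − 0.03 = 0.47. The difference falls from 20 to 17 points and power from 76.0% to 59.9%.
- *m*_A = 0.30, *m*_B = 0.10: 0.61 against 0.47. The difference is 14 points and power 43.2%.

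**4. The replacement rule.** Take the second row of the table (*m* 0.20 and 0.10, *t* = 0.7, true rate 0.5 in both arms), but treat the early leavers as drop-outs and replace them. The rate among those who stay is (0.5 − *m* × *t*)/(1 − *m*):
- Arm A: (0.5 − 0.14)/0.8 = 0.450.
- Arm B: (0.5 − 0.07)/0.9 = 0.478.

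The bias is −2.8 points, against +2 points if the same patients are carried forward. The text of {20c} allows either reading.

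**The case against.** **Safeguards exist.** Retrieval from records comes before carry-forward. Table 1 schedules a HAM-D17 at discharge, so an early leaver would normally carry a discharge score and not one from day 7 or 14. The older value arises mainly after withdrawal. The ±3-day window limits the problem to discharge before about day 25. These points stand and narrow the gap. They do not close it: a rating never made after discharge is unlikely to be in the records, and a discharge score is not a week-4 score.

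**The protocol does not say that patients leave early.** A reader might infer from "remain in the clinic after day 28 (±3 days" that the protocol expects some to be gone by day 28. It does not support that: the condition governs follow-up after day 28 and says nothing about leaving before it.

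**Dependence on outcome is not shown.** A reader might also infer that improved patients leave first and that the bias favours the intervention. The documents establish neither. Comparing discharge time between arms means that independence cannot be assumed; it does not demonstrate dependence. A score frozen at a good discharge rating and a score frozen before the drug has acted push in opposite directions.

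**The sizes are assumed.** This is correct. A normal approximation gives higher null rejection rates (7.0% at 3 points, 10.6% at 5 points), but the plan names Fisher's test. On that test a 3-point bias leaves the rate near the nominal 5%.

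**Imputation detail may belong in an analysis plan that is not shown.** True of finer detail, but {20c} already fixes carry-forward and replacement, and {18b} already states its conclusion.

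**Conclusion.** The point holds as a gap in the plan, not as a demonstrated bias. The inference in {18b} does not follow from its premise, and {20c} as written gives early leavers a different endpoint from the one defined. It also leaves open whether they are carried forward or replaced, and the two readings can move the result in opposite directions.

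Size and direction are unknown, since they depend on the share discharged before about day 25 in each arm and on how the last score relates to true week-4 status. Under the assumed differences of 10 to 20 points in early discharge, the response difference moves by about 2 to 8 points against a planned 20. Under equal shares and equal misclassification it does not move. Severity: should fix, before the data are analysed.

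**What to change.** **In {20c}:**
- For the primary endpoint, replace last value carried forward by multiple imputation of the day-28 HAM-D17 by arm, using HAM-D17 at days 0, 7, 14, 21 and discharge, and BDI-II. Derive response from the imputed score.
- Keep carried-forward and non-responder imputation as sensitivity analyses.
- State that every randomised patient, including those discharged early and drop-outs, stays in the primary analysis whether or not replacements are recruited.

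**In {18b}:**
- Delete the claim that loss is negligible, and report the number without a day-28 score by arm.
- Where feasible with existing raters, obtain the day-28 HAM-D17 by telephone after discharge.

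**Cost.** The imputation uses scores already scheduled, so it needs new wording and slightly more analysis work. It assumes that the scheduled scores account for who is missing, which is why the sensitivity analyses stay. The calls are a secondary option: their number depends on the unknown early-discharge share, and they may need extra resources. If recruitment is too far advanced for them, the analysis changes can still be made.
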